#### Intervention theoretical framework

The STHS program is based on the Social Ecological Model (SEM), a multifaceted framework for understanding the effects of personal, social, and environmental factors on behaviors (42). The SEM posits that individual behavior is shaped by multiple levels of influence (42), including individual, social, and environmental levels, which are common targets within healthy eating and physical activity interventions (43). At the individual level, STHS incorporates the theory of planned behavior (TPB) to promote healthy eating and physical activity. The TPB posits that strong behavioral intent increases the likelihood of an individual engaging in health behaviors (44), and behavioral intent is influenced by behavioral beliefs (e.g., knowledge and attitudes), social and subjective norms, and perceived behavioral control (44). Group discussions and interactive activities focus on improving behavioral beliefs, self-monitoring, and goal setting to increase perceived behavioral control, whereas group-based activities are utilized to change subjective norms about how peers engage in healthy eating and physical activity. On a social level, STHS activities emphasize civic engagement, including cultivating support for fellow students participating in physical activity and nutrition, establishing a shared purpose, mission, and vision for STHS, and building advocacy skills to promote positive changes in school physical activity and healthy eating environments. Finally, at the school level, students identify a beneficial change they can make to their school nutrition or physical activity environment and develop, implement, and evaluate that change.

#### Intervention implementation

The STHS program can be implemented before, during, or after school and is designed to be delivered by Extension Agents (Family and Community Health or 4H) or teachers. Once a school decides to participate, they will select a primary implementation lead—the school staff member or Extension Agent—and discuss who will provide additional implementation support, including the research team who will be available to substitute for the lead implementer, as needed. For the primary implementation lead(s), the research team will provide 1 hour of training, either online or in person. The training includes a curriculum overview, as well as information on additional resources (e.g., student workbook, classroom management resources), how to complete the fidelity checklist, student projects, and funding. The implementer will also receive a tote including all the small supplies they might need to deliver the curriculum (e.g., cones, cards, markers). Additional implementation support following the training will be provided, as needed, by the research team.

Additionally, for this study, the research team will recruit and train undergraduate university students to support curriculum delivery at intervention sites and ensure fidelity checklists are completed. Since STHS is being implemented across the state, student implementers are recruited from local colleges and universities as peer mentors who are closer in age to STHS student participants. Student implementers receive the same basic training provided to the implementation lead (described above); however, they also attend weekly check-in meetings with the research team. Meetings serve as a learning collaborative where all peer mentors discuss their successes and challenges with STHS implementation, provide updates on where they are in the implementation process, and provide feedback and support to one another. Additionally, student implementers participate in short trainings and discussions on various topics, including SMART goals, positive youth development, mentorship styles, etc. Finally, student implementers are reminded to work with their implementation leads to complete the fidelity checklists for each session that is complete. In the event that student implementers leave, a contingency plan has been developed to minimize interruptions or inconsistencies in curriculum delivery. We anticipate any interruption to be minimal since the students are not the primary implementers of the curriculum. Furthermore, our research team is fully trained in delivering the curriculum and will be able to step in to support curriculum delivery while another student is identified, hired, and trained.

### Measures

All student participant outcomes will be measured for student participants at both the intervention and delayed intervention control group schools within 1 month of the student recruitment period (T1), at the end of the school year or intervention period (T2), at the start of the next school year (T3), and at the end of the next school year (T4; Figure 1). Data collection sessions are estimated to take 45 minutes per student, and measures will be administered to students as a group. The two primary individual-level outcomes for this study are changes in MetS and positive youth development. Secondary individual-level outcomes include: (1) individual metabolic risk factors (blood pressure, fasting blood glucose, waist circumference, HDL cholesterol, and triglycerides); (2) body mass index percentile; (3) fruit and vegetable consumption; (4) accelerometer-derived physical activity, sedentary time, and sleep; and (5) cardiorespiratory fitness. Finally, other outcomes we will survey include TPB constructs related to nutrition and physical activity, nutrition- and physical activity-related behaviors, and youth's engagement with the school health environment. At the social level, we will assess students' perceptions of their peers' physical activity and healthy eating. At the environmental level, we will: (1) measure students' perceptions of the school health environment; (2) have school administration and staff complete a school environment assessment; and (3) conduct photovoice sessions. Student participants in both the intervention and the delayed intervention control group will receive a $50 gift card for each data collection session they complete (T1 to T4; $200 maximum for completing all sessions).

#### Individual-level outcome measures

##### Metabolic syndrome

Participants' MetS will be categorized dichotomously (yes or no) using the IDF definition of MetS for children and adolescents aged 10 to < 16 years old—abdominal obesity plus at least two of the four other MetS risk factors. The IDF uses the following criteria to define risk for each component: (1) waist circumference >90th percentile (i.e., abdominal obesity); (2) systolic blood pressure >130 or diastolic blood pressure >85 mmHg; (3) triglycerides >150 mg/dl; (4) high-density lipoprotein cholesterol (HDL-C) < 40 mg/dl; and (5) fasting blood glucose >100 mg/dl (45). Each risk factor will also be analyzed individually as a continuous variable as a secondary outcome.

Waist circumference will be measured using a medical-grade tape measure with Gulick spring attachment, and it will be measured at the midpoint between the floating rib and iliac crest. The measure will be performed three times and an average of the two closest measures will be used. Blood pressure will be measured using an automated Omron sphygmomanometer and an appropriately sized cuff on the children's upper right arm. As needed, participants will be asked to remove or pull up any bulky garments covering their upper right arm before testing begins. Participants will be asked to remain seated for 5 min before the measurement is taken. Blood pressure will be measured three times, and the two closest measurements will be averaged. For glucose, HDL-C, and triglycerides, participants will be directed to complete an overnight fast. A single capillary blood sample will be collected and inserted into a portable CardioChek Plus analyzer to measure triglycerides, HDL-C, and glucose. Only one measurement will be collected.

##### Positive youth development

We will measure positive youth development using the 5 C's Model of Positive Youth Development Scale-Short Form (PYD-SF) (46). The PYD-SF is a valid and reliable 34-item scale for youth 10–18 years old that assesses the strength of psychological, behavioral, and social development in youth. The five dimensions measured are (1) competence (sense of proficiency); (2) confidence (self-worth, self-efficacy); (3) character (adherence to societal and cultural rules); (4) connection (bonds with people and institutions); and (5) caring (sympathy and empathy toward others). Each positive youth development dimension will be calculated as a mean score, and the average across all dimensions will serve as the primary outcome.

##### Body mass index percentile

BMI percentile will be calculated using the standard formula and plotted on the Centers for Disease Control and Prevention (CDC) BMI-for-age clinical charts for the participants' corresponding sex. Height will be measured three times in succession to the nearest 1/8 inch using a portable SECA stadiometer (Seca Corporation, Hamburg, Germany). An average of the two closest measures will be used. Weight will be measured three times in succession to the nearest 0.1 pound using a portable Tanita body composition scale (Tanita Corporation, Tokyo, Japan). An average of the two closest measures will be used.

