#### Study setting

The study will take place in Texas, United States (US). Texas is the second most populous state in the country (30.5 million residents in 2023) and had the highest population increase of any state (473,000 new residents) in 2023 (14). Among Texas residents, 13.6% identify as non-Hispanic Black/African American, 39.8% as Hispanic/Latino, and 76.8% as White (14). Although state-level prevalence of MetS is not available, 21.5% of children 10–17 years old have obesity in Texas, one of the highest prevalences in the nation, stressing the importance of programs addressing MetS in this state (30). Furthermore, obesity rates are nearly twice as high for African American (26%) and Hispanic (29%) children as for Non-Hispanic White children (17%) (31).

The STHS program will be implemented in partnership with Texas A&M AgriLife Extension agents (32). Texas A&M AgriLife Extension is an education agency that provides programs, tools, and resources on a local and statewide level (33). AgriLife Extension has 250 offices (one in almost every Texas county), 900 extension educators, and a network of almost 100,000 volunteers that support the delivery of programs (33–35). Extension agents within the Family and Community Health and 4-H Youth Development units aim to help Texans better their lives through science-based educational programs designed to improve the overall health and wellness of individuals, families, and communities (36, 37). Agents deliver programs in the local communities (e.g., worksites, recreation centers, community events, military bases), as well as within local schools (36, 37).

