#### Quantitative analysis

We will use univariate and bivariate statistics to determine the distribution of outcome measures and to identify relevant covariates (75). To test between-group differences in post-intervention MetS and positive youth development, intervention and delayed intervention control group districts will be evaluated using a generalized linear model framework, in which the treatment group (intervention vs. delayed intervention control group) will be the primary independent variable, baseline score as a covariate, post-intervention score is the outcome, and district is a clustering variable (76). Other covariates (e.g., student sex), identified in the preliminary bivariate analyses, will also be included in the model. If missing data occurs, we will mitigate potential biases and loss of statistical power by analyzing multiple imputed datasets under an intention-to-treat approach (77). These analyses will be compared to per-protocol analyses to allow for the assessment of intervention effects under different conditions (78).

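### BMI percentile is the only BMI outcome named, and its scale shrinks differences in relative weight among the heavier students, where MetS is concentrated

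*Protocol article*

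**What the plan says.** All places are in the protocol article.

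- **Rank.** Measures lists BMI percentile among the secondary individual-level outcomes, as item "2) body mass index percentile".
- **Derivation.** The section Body mass index percentile states: "BMI percentile will be calculated using the standard formula and plotted on the Centers for Disease Control and Prevention (CDC) BMI-for-age clinical charts", by sex. No z-score, percent of a reference percentile or other BMI scale is named.
- **Timing.** Measures says: "All student participant outcomes will be measured for student participants at both the intervention and delayed intervention control group schools", at T1 to T4. The Design section describes T3 and T4 for the intervention group only. On either account both arms have T1 and T2, which is all this point needs.
- **Model.** Quantitative analysis describes one model, written for MetS and positive youth development: "baseline score as a covariate, post-intervention score is the outcome". No model is stated for BMI percentile.
- **MetS.** The entry criterion is "waist circumference >90th percentile (i.e., abdominal obesity", not BMI. On the components the section adds: "Each risk factor will also be analyzed individually as a continuous variable as a secondary outcome".
- **Where MetS occurs.** The Introduction gives MetS in 10.1% of adolescents aged 12 to 19 and in one in three of those who are overweight. Study setting says that 21.5% of children aged 10 to 17 "have obesity in Texas, one of the highest prevalences in the nation", and gives 26% and 29% for African American and Hispanic children.

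**The concern.** The trial aims to reduce MetS risk, and on the article's figures MetS is about 3.3 times as frequent in overweight adolescents as in adolescents overall (33.3 / 10.1). A percentile is a non-linear, bounded transform of relative weight. It is steep in the middle of the distribution and nearly flat at the top. A mean difference in percentile between arms is therefore driven mainly by mid-range students, and equal movement in heavier students counts for less. If the programme worked mainly in heavier students, the BMI outcome could show little or no effect although their relative weight had fallen.

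**Working it through.** The article gives no power or effect figure for BMI percentile, so there is none to reproduce. The check is on the scale itself.

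**1. Compression.** Assume that percentile = 100 × Φ(z), where z is the BMI-for-age z-score and Φ the standard normal distribution function. For a fall of 0.2 z, the loss in points is 100 × [Φ(z) − Φ(z − 0.2)]:

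| Start | z before → after | Percentile before → after | Points lost | Near-median loss ÷ this loss |
|---|---|---|---|---|
| Near median | 0.20 → 0.00 | 57.9 → 50.0 | 7.9 | 1 |
| 90th | 1.28 → 1.08 | 90.0 → 86.0 | 4.0 | about 2 |
| 95th | 1.64 → 1.44 | 95.0 → 92.6 | 2.4 | about 3.3 |
| 98.6th | 2.20 → 2.00 | 98.6 → 97.7 | 0.9 | about 9 |

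The local slope, 100 × φ(z) with φ the normal density, agrees. One z unit is worth 39.9 points at the 50th percentile, 17.5 at the 90th, 10.3 at the 95th and 2.7 at the 99th.

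**2. Does the form of the model matter?** In a change-score analysis the outcome is percentile after minus percentile before. In a baseline-adjusted analysis it is percentile after, with percentile before as covariate. Both express the treatment effect in percentile points, so the compression acts on both.

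**3. Likely effect on power (illustration only).** Inputs not in the article and therefore assumed: baseline BMI z normally distributed with SD 1.1, residual SD 0.3, 200 students per arm (20 students in each of 10 schools), clustering ignored, 1,500 simulated trials per setting. The mean was set so that 21.5%, 26% or 29% of students lie at or above the 95th percentile, borrowing the Study setting figures. Each trial was analysed by baseline-adjusted regression at two-sided 0.05, once on z and once on percentile:

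| Assumed effect | Power on z | Power on percentile |
|---|---|---|
| 0.08 z in every student | 75–76% | 62–65% |
| 0.16 z, only above the 85th percentile | 57–75% | 15–22% |
| 0.25 z, only above the 95th percentile | 43–64% | 8–9% |

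Ranges run over the three obesity shares. The absolute values depend on the assumptions. The direction holds in all nine settings, and the gap is widest when the effect is confined to heavier students.

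**The case against.** The case for leaving the plan alone has several sound parts.

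- **Change outcome.** A reader might infer that BMI percentile is analysed as a change score. The article does not say so. It applies that word to the primary outcomes ("The two primary individual-level outcomes for this study are changes in MetS and positive youth development"), and its only stated model uses the follow-up value adjusted for baseline. This stands as a matter of description but does not remove the problem (step 2).
- **Size.** A reader might infer that change in any student who could have MetS is almost invisible. The nine-fold ratio belongs near the 99th percentile. MetS entry is defined by waist above the 90th percentile, and at the 90th and 95th BMI percentiles the ratio is about 2 and 3.3. Change there is reduced, not erased. This stands.
- **Other adiposity measures.** Waist circumference, the measure that defines MetS here, is analysed as a continuous variable and has no percentile ceiling. This stands and limits the harm.
- **Population.** Students are not selected on weight, and the 21.5% to 29% are background rates, not those of the enrolled sample. Even at 29%, 71% of students would be below the obesity range, and their contribution to the arm difference is legitimate. This stands.
- **Power.** Under a uniform effect the illustrated loss is moderate. The large losses require an effect confined to heavier students, which the article does not state. This stands.
- **Yardstick.** Equal z is itself an imperfect measure of equal improvement in the far tail, which is why an extended z-score is suggested. The preference for a particular scale rests on general methodology, not on the documents. This bears on which scale to choose, not on whether the percentile saturates.
- **Left to the analysis plan.** The model for a secondary outcome may be specified elsewhere. The scale, however, is fixed in this article, so the point is open to comment.

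**Conclusion.** The point holds in a limited form. The article commits its only BMI outcome to a scale on which the same fall in relative weight counts about half as much at the 90th percentile as near the median, under a third as much at the 95th, and about a ninth as much at the 98.6th. An effect in heavier students is therefore under-weighted and power for this outcome is probably reduced, whichever of the two usual models is used. The compression figures rest only on the normal relation between percentile and z. The power figures rest on assumed SDs and effect patterns and show direction and rough size.

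It would be wrong to infer that the primary MetS result or the sample size is affected: BMI percentile enters neither, and the sample size is built on abdominal obesity. This is a minor, worthwhile improvement to one secondary outcome.

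**What to change.** State that BMI will be analysed on a scale that does not saturate, for example BMI as a percentage of the age- and sex-specific 95th percentile, or a BMI z-score with extended values above the 95th, with the baseline value on the same scale as covariate. Name one scale before outcome data are compared by arm. Keep BMI percentile and weight category as descriptive summaries.

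Height, weight, sex and date of birth are already collected, so no extra measurement, visit or participant is needed. The cost is a recalculation, rewording a named secondary outcome and possibly an update to its registry entry, which cannot be checked from the article.

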##### Fruit and vegetable consumption

We will use subdermal carotenoid levels as a proxy for fruit and vegetable intake. We will measure subdermal carotenoid levels using the Veggie Meter machine (Longevity Link Corporation, Salt Lake City, Utah, United States). The Veggie Meter is a non-invasive, portable machine that measures subdermal carotenoid levels using resonance Raman spectroscopy. The Veggie Meter provides an objective assessment of fruit and vegetable intake through a direct measure of dietary carotenoids and has been successfully used in school settings (47). Prior to taking the measure, participants will be asked to wash their hands or use an alcohol wipe to clean their non-dominant ring finger. The participant's non-dominant ring finger will be placed into the Veggie Meter finger slot, and the measure will be taken three times in succession. An average of the three measurements will be used.

##### Physical activity, sedentary time, and sleep

Physical activity, sedentary time, and sleep will be assessed using a triaxial Actigraph GT3x+ accelerometer (ActiGraph Corporation, Pensacola, Florida, USA). Participants will be instructed to wear the accelerometer on their non-dominant wrist for 24 h on seven consecutive days, and participants will only be asked to remove them for showers or activities where the devices could be submerged in water (e.g., swimming, bathing). Accelerometer non-wear time based on triaxial data was assessed using a validated algorithm (48). Participants who provide data for at least 16 h/day over a minimum of 3 weekdays and 1 weekend will be included in the analysis.

Accelerometer raw data will be collected at a frequency of 30 Hz, calibrated to local gravity, and expressed as Euclidean norm minus one using 5-s epochs. Time gaps identified as non-wear time through each 24-h interval that reached the validation criteria (≥16 h) will be imputed at the raw-data level based on average values across days. All valid days will be normalized to 24 h. Each epoch in a 24-h window will be classified as sedentary behavior (< 35.6 mg), light physical activity (≥35.6 and < 201.4 mg) or moderate-to-vigorous physical activity (≥201.4 mg) using the Hildebrand cut-off points recommended for children (49–51). Sleep time will be obtained using the Heuristic algorithm that examines the distribution of change in Z-angle. This algorithm differentiates sleep from other inactivity windows by calculating the longest sustained period of inactivity with the lowest number of interruptions in a 24-h time window (52). Time spent in moderate-to-vigorous physical activity, light physical activity, sedentary behavior, and sleep will be weighted according to weekdays and weekends (5:2 ratio) and averaged across days for each participant using a midnight-to-midnight day definition. The accelerometer data will be processed using the “GGIR” package version 2.9.1 in R software, version 4.3.0 (R Foundation for Statistical Computing, Vienna, Austria) (53).

##### Cardiorespiratory fitness

We will use the FitnessGram PACER multistage aerobic capacity test to assess cardiorespiratory fitness (VO2 max). After observing a demonstration, children will complete the test in groups of five or six. Children will run back and forth 20 m, with an initial running speed of 8.5 km/h and a progressive 0.5-km/h increase in running speed every minute. A research team member will lead the children through the test to provide instructions and pacing. As the test continues, it becomes progressively harder. The number of laps completed will be put into the standard prediction equations with their sex and age to estimate VO_2_ max.

##### Other measures

On the student survey, we will assess TPB psychosocial constructs—attitudes, subjective norms, perceived behavioral control—related to physical activity and healthy eating (54–56). We will also evaluate time spent being active at school, outside of school, and time spent being sedentary outside of school using the Youth Activity Profile (57). Related to healthy eating, students will complete the Texas School Physical Activity and Nutrition (SPAN) food frequency questionnaire that asks about how frequently they consume 20 different foods and ten drink categories. Responses will then be used to calculate the SPAN Healthy Eating Index and its subscales (healthy and unhealthy classifications) (58, 59). Finally, we will evaluate students' engagement with the school health environment using the Youth Engagement and Action for Health (YEAH!) survey (60). At baseline, sociodemographic variables will be collected and include questions on students' date of birth, sex (male, female, or not listed with the option to provide fill in their response), grade, Hispanic ethnicity (yes or no), race (American Indian, Asian, Black or African American, Native Hawaiian or Pacific Islander, White, or Other with the option to fill in their response).

